## Abstract

**Background:**

Adolescents in residential substance use treatment are at extremely high risk for relapse following discharge to the community. Parenting practices, including parental monitoring and parent-adolescent communication, have been established as key predictors of adolescent substance use outcomes and relapse. However, traditional office-based therapy may not be feasible for parents who face structural and systemic barriers. There is a clear need for effective, accessible, and scalable interventions for parents of adolescents receiving residential substance use treatment. In a prior pilot randomized controlled trial, we tested Parent SMART (Substance Misuse among Adolescents in Residential Treatment)—a technology-assisted parenting intervention informed by extensive formative research—as an adjunct to residential treatment as usual (TAU). Parent SMART demonstrated high feasibility and acceptability, as well as evidence of effectiveness in improving parental monitoring and communication.

**Objective:**

This protocol paper describes a fully-powered randomized controlled pragmatic effectiveness trial of Parent SMART as an adjunct to residential TAU. We hypothesize that families who receive Parent SMART will demonstrate greater improvements in parenting skills, reductions in adolescent substance use, and reductions in adolescent problem behaviors relative to families that receive residential TAU. We will test the exploratory hypothesis that reductions in adolescent substance use will be partially mediated by improvements in parenting skills.

**Methods:**

Adolescent-parent dyads (n = 220 dyads; 440 total) will be randomized to either residential TAU only or Parent SMART+TAU. Parents randomized to Parent SMART will receive access to a networking forum, an off-the-shelf computer program called Parenting Wisely, and up to four telehealth coaching calls. Multimethod follow-up assessments consisting of self-reported parent and adolescent measures, a parent-adolescent in vivo interaction task, and 8-panel urine screens will be conducted 6, 12, and 24 weeks postdischarge from residential care. Measures will assess parenting skills, adolescent substance use, and adolescent problem behaviors. Analyses will be conducted using latent change score structural equation modeling.

**Results:**

The trial was funded in August 2021; ethics approval was obtained in August 2020, prior to funding. Due to concerns with the administrative interface in the pilot trial, the Parent SMART networking forum is currently being rebuilt by a different vendor. The programming is scheduled to be completed by December 2021, with recruitment beginning in February 2022.

**Conclusions:**

The proposed research has the potential to advance the field by serving a high-need, underserved population during a vital treatment juncture; targeting parenting practices (putative mediators) that have been shown to predict adolescent substance use outcomes; addressing barriers to accessing continuing care; and testing a highly scalable intervention model.

**Trial Registration:**

ClinicalTrials.gov NCT05169385; https://clinicaltrials.gov/ct2/show/NCT05169385

**International Registered Report Identifier (IRRID):**

PRR1-10.2196/35934

## Introduction

### Background

Adolescents with substance use disorders requiring a residential level of care typically present with severe symptoms and an array of co-occurring mental health, behavioral, motivational, legal, and environmental problems [1,2]. While a number of studies have found that residential treatment is associated with an acute reduction in symptoms and co-occurring problems [3,4], long-term outcomes of this population are far less encouraging [5]. Longitudinal studies indicate that the majority of adolescents will relapse within 90 days of discharge [6]. Such poor outcomes are likely at least partially attributable to the fact that only about 35%-45% of adolescents receive any continuing care [7,8].

To improve adolescent outcomes, it has been argued that continuing care interventions should move beyond solely including the adolescent to actively targeting parent engagement. Multiple systematic and meta-analytic reviews [9-12] have demonstrated that substance use interventions that include parents significantly outperform adolescent-only approaches. In recognition of this empirical support, the Residential Care Consortium released a white paper advocating that residential programs improve parent engagement, particularly prior to and following discharge to the community when disruptions in care are common [13]. Further research has suggested that adolescent substance use interventions targeting parental monitoring and communication, two key parenting processes that are protective against adolescent substance use [14,15], are associated with better adolescent outcomes than interventions targeting parent education only [16-18].

Building upon the extant research highlighting how positive parenting skills protect against adolescent substance use [19-21], as well as the research demonstrating the challenges with parent engagement in traditional office-based sessions [22,23], we developed a technology-assisted parenting intervention called Parent SMART (Substance Misuse among Adolescents in Residential Treatment). Parent SMART was designed as an adjunct to residential treatment for adolescents with substance-related problems. It consists of three elements—an online parent skills program, a parent networking forum, and telehealth coaching sessions. The online parenting skills program is an off-the-shelf product [24,25], whereas the networking forum and telehealth coaching sessions were specifically designed in response to formative research with parents of adolescents in residential treatment [26].

We previously tested the Parent SMART intervention via a pilot randomized controlled trial with 61 parent-adolescent dyads across two residential programs (one acute care and one standard residential care) [27]. Results of the pilot trial met or exceeded all of the recruitment, retention, acceptability, feasibility, and fidelity benchmarks established a priori as evidence that the intervention was worthy of further study in a larger trial. Parent SMART demonstrated excellent acceptability and feasibility, with parents who received Parent SMART reporting significantly higher levels of satisfaction and greater likelihood of recommending the services they had received than those who received residential treatment alone [27]. In addition, Parent SMART was associated with significant improvements in parental monitoring and communication, measured via both self-report scales and a behavioral intervention task, across both residential settings [28]. Among adolescents in the acute care setting, Parent SMART was also associated with significant reductions in days of binge drinking and school-related problems; we were underpowered to detect differences in the standard residential care setting, but a number of significant time effects were observed, revealing encouraging reductions in days of substance use, substance-related problems, and high-risk behaviors among adolescents in both conditions [27]. Building upon this prior work, the current protocol describes a fully-powered, randomized controlled trial testing the effectiveness of Parent SMART as an adjunct to residential TAU on parenting skills, adolescent substance use, and problems commonly related to substance use such as school truancy, externalizing behavior, sexual risk behavior, and criminal involvement [10]. A conceptual overview of the study’s specific aims is presented visually (Figure 1) and elaborated upon as follows.

**Figure 1 figure1:**
[figure not shown]
Overview of protocol aims. Parent SMART: Substance Misuse in Adolescents in Residential Treatment.

### Specific Aims

**Primary aim 1:** Evaluate the effectiveness of Parent SMART+TAU versus TAU on proximal parenting outcomes. Hypothesis 1 is that, relative to those in TAU, parents receiving Parent SMART+TAU will exhibit greater improvements in parental monitoring and communication at 6, 12, and 24 weeks postdischarge from residential care.

**Primary aim 2:** Evaluate the effectiveness of Parent SMART+TAU versus TAU on distal adolescent substance outcomes. Hypothesis 2 is that, relative to those in TAU, adolescents whose parents receive Parent SMART+TAU will show greater reductions in the proportion of days substances were used outside a controlled environment and substance-related problems at 6, 12, and 24 weeks postdischarge from residential care.

**Secondary aim:** Evaluate the effectiveness of Parent SMART+TAU versus TAU on distal adolescent problem behavior outcomes commonly related to substance use: school problems, externalizing behaviors, sexual risk behavior, and criminal involvement. Hypothesis 3 is that adolescents whose parents receive Parent SMART+TAU will have greater reductions in a range of problem behaviors, including school truancy, externalizing behavior, risky sexual behavior, and criminal involvement at 6, 12, and 24 weeks postdischarge from residential, relative to adolescents in TAU.

**Exploratory aim**: Evaluate the extent to which change in parenting processes mediates change in adolescent substance outcomes. An exploratory hypothesis is that change in parenting processes (ie, communication, monitoring) at 6-weeks postdischarge from residential care will partially mediate primary adolescent substance use outcomes at 12 and 24 weeks.

## Methods

### Study Design and Ethical Considerations

Parent-adolescent dyads will be assigned to receive either residential TAU or Parent SMART+ residential TAU on a 1:1 schedule using a two-arm, parallel-group, randomized trial design. The Brown University Institutional Review Board has approved all study procedures described herein (ID# 2006002748). The study is registered in clinicaltrials.gov (NCT05169385). The timing of key study elements, including randomization and parent-adolescent assessments, is depicted in Table 1.

**Table 1 table1:** Timing of key protocol elements.

		Residential treatment					Postdischarge period		
Timepoint		Enrollment	Baseline assessment	Allocation	Residential stay (2-45 Days)	6 weeks		12 weeks	24 weeks
**Enrollment**									
	Informed consent/assent	X							
	Masked allocation			X					
**Control condition**									
	Residential treatment as usual				X				
**Parent SMART condition**									
	Parenting Wisely program				X	X		X	
	Parent networking app				X	X		X	
	Telehealth coaching sessions				X	X			
**Assessment of primary aim 1**									
	Parental monitoring questionnaire		X			X		X	X
	Parental communication questionnaire		X			X		X	X
	Family assessment task		X			X		X	X
**Assessment of primary aim 2**									
	Proportion days used substances		X			X		X	X
	Substance-related problem scale		X			X		X	X
	Urine screens					X		X	X
**Assessment of secondary aim**									
	School-related problem scale		X			X		X	X
	Behavioral complexity scale		X			X		X	X
	Risky behavior scale		X			X		X	X
	Crime and violence scale		X			X		X	X

### Inclusion Criteria

A total of 440 participants—220 parent-adolescent dyads—will participate in this trial. Parent inclusion criteria are: (1) parent or legal guardian of adolescent aged 12-18 years admitted to residential treatment due to concerns about substance use; (2) will be primary guardian living with adolescent after their discharge from residential treatment; (3) fluent in English or Spanish; and (4) willing and able to complete a structured assessment prior to the adolescent’s discharge from residential treatment. Adolescents whose parents qualify are eligible to participate as long as they are willing to participate in the research and able to complete a structured assessment prior to their discharge from residential treatment.

### Recruitment

Parents will be referred to the study via a residential intake coordinator at the partner facility (see residential TAU), who will briefly inform parents about the study during the intake process. Interested parents will be given a consent to contact form on a study tablet to review and sign. The consent to contact form will provide a brief overview of the study and will collect the parent’s preferred contact information so that research staff can contact the parent at a later time. The research staff will then contact the parent to describe the study risks and benefits and complete a brief eligibility screener. Interested parents who qualify will provide informed consent to participate using electronic consent forms; parents of adolescent minors will also provide informed parental consent for their child to participate. The research staff will then work with staff at the residential facility to schedule a time to speak with the adolescent via phone or Zoom to describe the study and to complete a brief screener. Interested adolescents will provide informed assent (for those age 13-17 years) or informed consent (for those age 18 years) via electronic forms. Parents and adolescents must independently provide consent and assent, respectively, for an adolescent-parent dyad to enroll in the study.

### Anticipated Participant Demographics

Based on the participants enrolled in the pilot trial [27], parents are expected to be predominantly biological mothers (about 80%), with the remainder comprised of biological fathers, adopted parents, and other legal guardians. For adolescent characteristics, we expect approximately 10% of adolescents to identify their gender as nonbinary, with the remainder identifying as male (45%) or female (45%). We anticipate about 25% of adolescents will identify as Hispanic. We expect adolescents to self-identify in the following racial categories: White (65%), Black or African-American (12%), Multiracial (15%), and Asian or Asian American (2%). We expect about 6% of adolescents to select “prefer not to answer” as their preferred race.

### Randomization

Parent-adolescent dyads will be randomized immediately after completing the baseline assessment using the urn randomization method [29], which systematically biases randomization in favor of balance across conditions. Dyad randomization will be balanced according to adolescent biological sex at birth (male vs female), planned length of stay in residential (0-10 days vs 10+ days), and parent’s preferred language (English vs Spanish). Random assignments will be made using an Excel urn generator developed by Stout and colleagues for Project MATCH [22]. Parents will be informed about their treatment assignment shortly after randomization. Residential staff and study research staff conducting follow-up assessments will be blind to the condition.

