### Interventions

#### Residential TAU

TAU consists of the standard residential services offered to adolescents at our partner facility and will be received by families in both conditions. The partner residential treatment program, Rosecrance Health Network, offers residential treatment for adolescents at two locations, one in Rockville, Illinois, and one in Sioux City, Iowa. Length of stay ranges from 2 to 45 days, depending on the adolescent’s level of need and insurance coverage. Adolescents at Rosecrance Health Network receive about 15 hours of educational programming and 25 hours of treatment per week in a predominantly group-therapy model based on dialectical behavioral therapy [30]. Each adolescent is also assigned a primary counselor who checks in with them at least twice per week. Medication management is offered by a nurse practitioner or psychiatrist as needed. Prior to discharge, parents receive standard discharge planning, which consists of a customized relapse prevention plan as well as either a referral to a new outpatient therapy provider or a return to a prior outpatient therapy provider. Families receive referrals to a psychiatrist or local self-help group as indicated. Postdischarge, families are encouraged to phone the intake coordinator for further referrals or support.

Following randomization, parents will be given an educational pamphlet about adolescent substance use, parenting skills, and local community resources, consistent with usual resource provision at the partner site.

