##### Covariates: Demographics

Parent and adolescent sociodemographics will be assessed and controlled for as covariates. Parents will complete a routine sociodemographic form. Adolescents will complete the GAIN Background section, which collects routine sociodemographic variables including age, sex, gender identity, ethnicity, race, and grade in school. Items in other GAIN sections indicate the adolescent’s history of substance use or mental health treatment utilization, data that will be used to control for treatment received.

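### The urn balances on planned length of stay and parent language, but among the urn factors the stated covariates name only sex; the two length-of-stay levels also both contain day 10

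*Protocol article*

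**What the plan says.** **Allocation.** The Randomization section uses an urn scheme that "systematically biases randomization in favor of balance across conditions". It names three factors:
- "adolescent biological sex at birth (male vs female")
- "planned length of stay in residential (0-10 days vs 10+ days")
- the parent's "preferred language (English vs Spanish")

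The Residential TAU section adds that "Length of stay ranges from 2 to 45 days" and ties the duration to level of need and to insurance.

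**Adjustment.** The section Covariates: Demographics says "Parent and adolescent sociodemographics will be assessed and controlled for as covariates". For parents it says only "Parents will complete a routine sociodemographic form", without listing the items. For adolescents it refers to "routine sociodemographic variables including age, sex, gender identity, ethnicity, race, and grade in school". It adds that GAIN items on past treatment will serve as an adjustment for care received. The Data Analysis Plan overview and the limitations paragraph add contact time (modules, posts or app time, and coaching sessions). None of these places names planned length of stay or preferred language, and none says that the randomisation factors enter the models.

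**The concern.** When allocation is pushed towards balance on a variable that predicts outcome, the treatment difference varies less from one randomisation to the next than it would under simple randomisation. A model without that variable does not see this. It leaves the variable's contribution in the residual variance, so the reported standard error is somewhat too large. The usual principle is therefore to analyse by the factors used to allocate.

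Planned length of stay is the clearest gap. It is a balancing factor, it is in no stated covariate list, and the article's own link between stay and level of need makes it plausibly prognostic. At stake are confidence intervals a little wider than the design earns and some power forgone.

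A second, smaller matter is that the two length-of-stay levels share a boundary value, so one attainable planned stay has no unique level as written.

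**Working it through.** **1. Urn factors set against the stated covariates.**

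| Urn factor | In a stated covariate list? |
|---|---|
| Sex at birth | Yes: sex is named in the GAIN Background items |
| Planned length of stay | No: the past-treatment items concern care received, not the stay planned at allocation |
| Parent's preferred language | Not named; covered only if the parent form records it |

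**2. The plan's own power figure.** Inputs from the Power section are 220 dyads, 0.38 SD, alpha 0.05 and 80% power. Allocation is 1:1, so 110 per arm. Sidedness is not stated; two-sided is assumed.
- Standard error of the difference in SD units: sqrt(2/110) = 0.1348.
- Power: Phi(0.38/0.1348 - 1.96) = Phi(0.858) = 0.805. The two-sample t-test gives 0.801.
- Sample size for 80% power: 2 x (1.96 + 0.842)^2 / 0.38^2 = 108.7, so 109 per arm and 218 in total.
- Smallest detectable effect: (1.96 + 0.842) x 0.1348 = 0.378 SD (0.379 by t-test).

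The stated figure reproduces, and it takes no credit for covariates.

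**3. Upper bound on the effect of omission.** If balance on the omitted factors were perfect and they explained a share R2 of outcome variance, the unadjusted standard error would be too large by 1/sqrt(1 - R2), and the true type I error would be 2 x (1 - Phi(1.96/sqrt(1 - R2))).
- R2 = 0.05: ratio 1.026, type I error 0.044.
- R2 = 0.10: ratio 1.054, type I error 0.039.
- R2 = 0.20: ratio 1.118, type I error 0.028.

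An urn only leans towards balance, so these figures overstate the effect.

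**4. Simulation of the urn.** The settings were n = 220, three binary factors and 4,000 runs per cell. A linear model was fitted to one continuous outcome, without and with the three factors. Length of stay and language share R2 equally; sex has no effect. The assumed prevalences are 50% for sex, 50% for length of stay and 15% for Spanish. Neither R2 nor the prevalences come from the article.

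| Assumed R2 | Type I error, without / with | Power at 0.38 SD, without / with | Power forgone (points) |
|---|---|---|---|
| 0 | 0.049 / 0.052 | 0.804 / 0.801 | none |
| 0.05 | 0.045 / 0.049 | 0.803 / 0.817 | 1.4 |
| 0.10 | 0.044 / 0.050 | 0.807 / 0.837 | 3.0 |
| 0.20 | 0.041 / 0.053 | 0.815 / 0.883 | 6.8 |

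The Monte Carlo standard error is about sqrt(0.05 x 0.95/4000) = 0.003 for type I error and sqrt(0.8 x 0.2/4000) = 0.006 for power. At R2 = 0.20 the simulated type I error of 0.041 is clearly above the perfect-balance value of 0.028, so the bound in step 3 should not be quoted as the expected effect. Without the factors, power stays at or just above 80% in every row.

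**5. The boundary.** In whole days, the levels 0-10 and 10-45 intersect in exactly one value, 10. Stays run from 2 to 45 days, so that value can occur.

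**The case against.** The strongest reply is that this is an argument from silence. The covariate section sits among the assessments and does not claim to be a complete model specification. A condensed article commonly leaves that specification to the full protocol or the SAP, which are not shown and may already include the urn factors. That stands in part. A reader might infer that the trial will ignore its randomisation factors in the analysis, and the article does not support that: sex is a named covariate, language may be on the parent form, and nothing excludes planned length of stay. What remains is that the article does give an adjustment set, in several places, and a variable used to allocate is missing from it.

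A second reply is that the size is assumed. This also stands. No R2 is given, and what counts is the variance explained beyond the sociodemographics and the baseline outcome. Because the models work on change from baseline, part of the severity that planned stay reflects is already absorbed, which favours the lower end of the range.

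A reader might also argue that planned stay must be adjusted for because it determines how much of the 90-day recall at 6 weeks precedes admission. That does not support the fix: the overlap depends on actual stay, and a two-level planned-stay covariate would not correct it.

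On the boundary, 10+ beside 0-10 is easily read as more than 10, and the generator needs one category per dyad in any case. That is a fair reading, but the text does not state it.

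**Conclusion.** The point holds as a modest matter of efficiency and consistency. Planned length of stay is balanced in the urn and is absent from every stated covariate list; the coverage of language cannot be determined from the article.

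If the omitted factors explain 5-20% of outcome variance beyond the covariates already in the model, the test runs at about 0.045-0.041 instead of 0.05, and about 1-7 points of power at 0.38 SD are forgone. These figures rest on the assumed R2 and prevalences, a two-sided test, and a linear model standing in for the latent change score model. If the factors do not predict outcome, nothing is lost.

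Two stronger conclusions are tempting and unsupported. Omission does not bias the treatment effect or inflate type I error; the error is on the conservative side. Nor does it undermine the stated 80% power, which reproduces without any covariate gain; the power forgone is precision above that figure.

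The overlap at 10 days is real as written but minor. Planned stay is fixed before allocation, so allocation stays random under either coding; at worst, balance is slightly looser for a few dyads.

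**What to change.** State that sex at birth, planned length of stay and parent's preferred language, coded exactly as entered in the urn, are fixed covariates in every primary and secondary model. If the SAP already says so, a cross-reference is enough.

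Rewrite the length-of-stay levels so that each whole number of days belongs to one level only, and make the wording agree with the coding in the urn generator.

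The cost is a line in the analysis plan and a line in the randomisation description. All three variables are known before randomisation, so no new data are needed, and two or three extra model terms with 220 dyads cost almost nothing: in the simulation with R2 = 0, power was 0.801 with the factors and 0.804 without, which is within simulation error.
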